### 8.2.7 Interim analysis

The study will be conducted according to a two-stage group sequential test design with possible sample size adaptation after the interim analysis. The interim analysis is planned after observation of 31 deaths (expected observation time of 11.1 months). No per-protocol analysis will be performed for the interim evaluation of efficacy and safety.

At the planned interim analysis, the random code of the subjects to be included in the interim analysis will be unblinded by a member of the DMSC. Before unblinding a Statistical Analysis Plan will be prepared for the interim analysis by the unblinded statistician and agreed on between the sponsor and the unblinded statistician. The unblinded statistician will electronically match the random code with the study data and will send confidentially the results and a brief statistical report summarising the results of the interim analysis to the DMSC.

### 8.2.8 Other evaluations

#### **Subgroup Analyses**

Subgroup analyses will be performed for the bulbar and spinal stratum.

#### **Multicentre Data**

Exploration of possible heterogeneity of treatment effects across centres will be performed in a descriptive manner if appropriate, e.g. by graphical display of the results of the individual centres.

To assess the homogeneity of treatment differences across centres for the primary efficacy variable, treatment-by-centre interaction will be evaluated.

## **8.3 Data handling and record keeping**

The investigator must maintain all study records, patient files and other source data for the maximum period of time permitted by the hospital or institution. The data from the individual centre will be transferred to the coordinating centre. They will be monitored at the site and with the help of source documents.

Data processing will be conducted on the basis of the Data Management Plan approved by the sponsor prior to any data management activity. The data cleaning process will be performed according to the Data Validation Plan. The database will be designed by acromion GmbH using the acromion DMS based on Sybase.

Data will be entered into the database using the technique of independent double data entry with a third person-compare where two people enter the same data independently and a third person resolves any discrepancies. Changes made to the data will be documented in an audit trail.

The following international dictionaries will be used for medical coding in their current installed version at the beginning of coding activities, ensuring that there is only one version used during the study:

- Diseases: Medical Dictionary for Regulatory Activities (MedDRA)
- Adverse events: Medical Dictionary for Regulatory Activities (MedDRA)
- Drugs: WHO-DRL dictionary

The statistical analysis will be performed using the software package SAS version 9.1 (SAS Institute Inc., Cary, NC 27513, USA).

All available data will be included in the analyses and will be summarized as far as possible. Unless otherwise specified there will be no substitution of missing data, i.e. missing data will not be replaced, missing data will be handled as 'missing' in the statistical evaluation.

In the case of a premature termination, the last available observation will be used for analysis (LOCF approach), if applicable and considered reasonable. Missing baseline data will not be replaced. A more detailed description of the handling of missing data will be provided in the statistical analysis plan after review of the data for the interim and the final analysis.

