### **3 STUDY PURPOSE, TRIAL OBJECTIVES AND ENDPOINTS**

As the efficacy of riluzole to prolong survival in ALS is limited, there is an urgent need to identify other compounds and to evaluate their potential in clinical studies. The pharmacological profile of pioglitazone suggests that this compound may be effective in slowing down the neurodegenerative process observed in ALS and it is therefore important to study this drug in ALS patients. As a significant percentage of patients with ALS will receive riluzole, the study population will consist of patients stabilised on standard riluzole therapy at time of inclusion. After completing this study, patients may have the option to participate in another planned, longer, safety study with pioglitazone.

This study will evaluate the efficacy, safety and tolerability of pioglitazone (45 mg/day) versus placebo in patients with ALS receiving standard, approved therapy (riluzole, 50 mg bid). Mortality defined exclusively as death represents the primary endpoint. Secondary efficacy endpoints will include incidence of tracheotomy or non-invasive ventilation (NIV), ALS Functional Rating Scale (ALSFRS-R; the revised version including the respiratory parameters) and measurement of quality of life using the Euroqol EQ-5D. Assessment of clinical tolerability and safety will be performed by comparison of findings on physical examination, adverse events incidence, and clinical laboratory values across treatment groups.

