## **7.6 Premature discontinuation / Patient replacement**

Each patient can at any time withdraw from the study without personal disadvantages and without stating reasons.

Whenever possible, all patients prematurely discontinuing study medication will continue to be followed and complete all scheduled evaluations for the duration of the study. The reason(s) for premature cessation of a patient's participation during the trial, other than death, should be specified on the case report form. Whenever possible the evaluations scheduled for the end of the treatment period should be performed.

Study treatment may be stopped prematurely if any of the following events occur, according to the judgement of the investigator:

- Significant intolerance of the study medication, or significant clinical or laboratory findings, e.g. increase in ASAT or ALAT >2.5 upper limit of normal
- Significant intercurrent illness or emergency situation requiring cessation of the study
- The patient wishes to terminate his/her participation in the study
- Investigator judgement that it is in the best interest of the patient
- Failure to comply with the investigational procedures
- Pregnancy
- Technical reasons (change of physician, change of address of volunteer/patient)

Patients who have started double-blind treatment will not be replaced.

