## 8.2 Statistical methods

A Statistical Analysis Plan describing all details of the analyses to be performed will be prepared by the study statistician and approved by the sponsor prior to the start of statistical analysis. The recommendations of the ICH E9 Note for Guidance on Statistical Principles for Clinical Trials (CPMP/ICH/363/96, 1998) will be taken into account.

The primary endpoint will be subjected to a confirmatory analysis. All secondary and safety parameters will be evaluated and reported descriptively.

All individual data as well as results of statistical analyses – whether explicitly discussed in the following sections or not – will be presented in individual subject data listings and statistical summary tables.

Continuous variables will be summarised using the following standard descriptive summary statistics: number of observations, arithmetic mean, standard deviation, minimum, lower quartile, median, upper quartile, maximum. In addition, geometric mean and coefficient of variation derived from log-normally distributed data will be calculated for serum concentrations. Categorical data will be described using absolute and relative frequencies.

A more detailed elaboration of the principal statistical features stated in this protocol will be provided in the statistical analysis plan, which will be finalized prior to unblinding of the database. The statistical analysis plan will take into account any amendment to the study protocol.

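### LOCF after premature termination has no exception for death, so ALSFRS-R and EQ-5D summaries would be biased towards the arm with more deaths

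*Protocol*

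**What the plan says.** Section 8.3 of the protocol sets a default and then an exception. The default is: "Unless otherwise specified there will be no substitution of missing data, i.e. missing data will not be replaced". The exception is: "In the case of a premature termination, the last available observation will be used for analysis (LOCF approach), if applicable and considered reasonable". Further detail "will be provided in the statistical analysis plan after review of the data for the interim and the final analysis". Section 8.2 limits that timing, because it describes the SAP as a document "which will be finalized prior to unblinding of the database".

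The rule does not mention death. The nearest text is in Section 7.6: "The reason(s) for premature cessation of a patient's participation during the trial, other than death, should be specified on the case report form". Death is exempted there only from having its reason recorded, which implies that it counts as a premature cessation. The protocol does not say how a functional or quality-of-life score is handled after death.

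The endpoints exposed to the rule are the "ALS Functional Rating Scale (ALSFRS-R; the revised version including the respiratory parameters) and measurement of quality of life using the Euroqol EQ-5D", two of the three secondary efficacy variables. Section 8.2 has all secondary parameters reported descriptively.

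**The concern.** LOCF assumes that a patient's score would have stayed where it was last seen. ALS progresses, and a patient who dies has not kept the last recorded level of function. If the rule is applied to deaths, each death stops the recorded decline at the last visit before it. The arm with more or earlier deaths then accumulates less recorded decline and looks better preserved.

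If pioglitazone prolongs survival as the sample size assumes, the secondary tables would show it apparently worsening function even when it has no effect on function. If it shortened survival, the tables would make it look protective. A descriptive estimate with a systematic error of known direction can still mislead whoever reads it beside the survival result.

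**Working it through.** **Inputs from the protocol.** 18-month survival 60% (placebo) and 78% (pioglitazone), 10% drop-out allowance, 198 subjects inflated to 220, loss to follow-up below 1% in four earlier trials and expected again (Section 8.1). 110 patients per arm (Section 1). ALSFRS-R at baseline and months 1, 2, 3, 6, 9, 12, 15 and 18; EQ-5D at baseline and months 2, 6, 12 and 18 (schedule of study procedures).

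**Assumptions, not in the documents.** Exponential survival; linear ALSFRS-R decline at the same rate in both arms, 0.5 or 1 point per month.

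**The plan's own figures.** The hazard ratio is ln 0.78 / ln 0.60 = 0.486, as stated. The Schoenfeld formula gives 61 deaths. With critical values 2.797 and 1.977 at information 0.5 and 1, one-sided alpha is 0.025 and power at 61 deaths is 80.1%. 198 / 0.9 = 220. The survival inputs are therefore coherent and can be used here.

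**How much is missing because of death.**
- Placebo: 110 × 0.40 = 44 deaths by month 18.
- Pioglitazone: 110 × 0.22 ≈ 24 deaths.
- Together about 68 of 220 patients, or 31%.
- The full drop-out allowance is 220 − 198 = 22 patients. Loss below 1% would be about 2. Under either figure death is the larger source of missing late scores.

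**Mean month of the last ALSFRS-R observation.** With S(t) = 0.60^(t/18) or 0.78^(t/18), the mean last observed month is

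S(1) + S(2) + S(3) + 3 × [S(6) + S(9) + S(12) + S(15) + S(18)].

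- Placebo: 0.972 + 0.945 + 0.918 + 3 × (0.843 + 0.775 + 0.711 + 0.653 + 0.600) = 13.58 months.
- Pioglitazone: 0.986 + 0.973 + 0.959 + 3 × (0.920 + 0.883 + 0.847 + 0.813 + 0.780) = 15.65 months.

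**Spurious gap in mean month-18 change, true difference zero.**

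| Assumed decline | Placebo | Pioglitazone | Gap (pioglitazone − placebo) |
|---|---|---|---|
| 0.5 point/month | −6.8 | −7.8 | −1.0 |
| 1 point/month | −13.6 | −15.7 | −2.1 |

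Per patient who dies, the mean time frozen is (18 − 13.58)/0.40 = 11.0 months on placebo and (18 − 15.65)/0.22 = 10.7 months on pioglitazone. That equals about 11 points only if the decline is 1 point per month; at 0.5 it is about half.

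**Sensitivity.** A simulation with 200,000 patients per arm allowed slopes to vary between patients (baseline 38, SD 5; mean decline 0.5, 1.0 or 1.5 points per month, SD half the mean) and gave none, a moderate or a strong link between fast decline and death. With the same distribution of decline in both arms, the LOCF gap was negative in all nine scenarios:
- −1.0 to −1.4 at 0.5 point per month;
- −2.1 to −2.9 at 1.0;
- −2.7 to −3.8 at 1.5.

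Two alternatives were examined in the same runs:
- The simple month-18 mean among survivors showed almost no gap when decline and death were unrelated, but −0.5 to −2.0 when they were linked. Dropping LOCF and comparing survivors' means is therefore not a full remedy.
- Scoring deaths as zero reversed the sign, to between +1.4 and +5.3. The handling of death alone can decide which arm looks better.

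EQ-5D was not simulated. The same direction follows if the score worsens with progression.

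**The case against.** The strongest reply is that the protocol never says dead patients will be given a living score. Death reaches the rule only by inference from Section 7.6. Sections 5.5 and 7.6.1 connect early termination with a final examination, which requires a living patient, and LOCF applies only where it is judged reasonable, so a SAP could decline it for deaths. This stands as a limit on certainty. It does not remove the point: the protocol names a method, excludes nothing from it, and gives no criterion for when it is reasonable.

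It is also fair that the protocol fixes no month-18 contrast for these scores, so the gaps above illustrate the rule rather than reproduce a planned table, and that the decline rates are assumed.

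Three stronger readings are tempting and are not supported:
- **That Section 8.3 contradicts itself.** A reader who sees only "missing data will not be replaced, missing data will be handled as 'missing' in the statistical evaluation" might think so. The sentence opens by allowing for exceptions, and LOCF is the specified exception.
- **That the rule could be chosen after seeing results by arm.** The phrase about writing the detail after data review might suggest this. Section 8.2 has the SAP final before unblinding, Section 6.10.2 breaks the code only after the database is frozen, and Section 8.2.7 requires an interim plan before the interim unblinding. The text describes a blinded review.
- **That a dead patient keeps a positive EQ-5D utility.** The protocol does not specify a utility index, so neither that statement nor a utility of zero at death can be read into it.

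Finally, a joint rank or a worst score for death carries the survival effect into the secondary result. That answers a different question and is not a neutral correction.

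**Conclusion.** The point holds for the descriptive secondary endpoints. As written, LOCF would apply mainly to deaths, and in a declining disease it favours the arm with more of them. With identical decline in both arms and the protocol's survival rates, the artefact is about 1.0 ALSFRS-R point at 0.5 point per month and 2.1 points at 1 point per month, against pioglitazone if survival improves as planned. The direction is stable across the scenarios tried. The size depends on the assumed decline rate and on LOCF being applied to deaths. The log-rank test, alpha, power and sample size are untouched, and under the planned survival effect the bias cannot create a false claim of benefit. The sponsor should change this, but it does not threaten the trial's main conclusion.

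**What to change.** In Section 8.3, remove LOCF for ALSFRS-R and EQ-5D, then:

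- **ALSFRS-R:** linear mixed model for rate of decline on all observed visits, with random intercept and slope, adjusted for onset stratum (bulbar or spinal).
- **EQ-5D:** summarise from observed visits, with no value carried past death.
- **Deaths:** state explicitly how they enter both endpoints, before the interim code is opened. A joint rank of survival and function may be added as a sensitivity analysis, labelled as answering a combined question.

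The cost is protocol and SAP wording and slightly more analysis. No extra data are needed, because the visits are already scheduled. The mixed model relies on a missing-at-random assumption, and it estimates decline as if follow-up had not been cut short by death; the report should say so.

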## **9 ETHICAL ASPECTS**

This protocol is in accordance with the principles laid down by the 18th World Medical Assembly (Helsinki, 1964) and its amendments laid down by World Medical Assemblies. This protocol is also in accordance with laws and regulations of the country in which the trial is performed, as well as any applicable guidelines. It is the responsibility of the investigator to obtain informed consent in compliance from each patient prior to entering the trial or, where relevant, prior to evaluating the patient's suitability for the study.

### **9.1 *Independent Ethics Committee Approval***

Before implementing this study, the protocol, the proposed informed consent form and other information to subjects, must be reviewed by a properly constituted Independent Ethics Committee / Institutional Review Board (IEC/IRB). A signed and dated statement that the protocol and informed consent have been approved by the IEC/IRB must be given to the sponsor before study initiation. The name and occupation of the chairman and the members of the IEC/IRB must be supplied to the sponsor.

### **9.2 *Informed Consent***

The investigator must ensure that before enrolment in the study, all eligible patients are given detailed information both orally and in writing, about the following points in particular:

- Aims, duration and methods of the study
- Risks, anticipated benefits and potential hazards according to our current knowledge

- That he or she is free to withdraw his or her consent at any time without affecting subsequent treatment or his/her relation with the doctor
- That the clinical research monitors and auditors appointed by the sponsor, Health Authority Inspectors and IEC/IRB members have access to the clinical source data about them.

Informed consent must be given by a standard written declaration drafted in simple non-technical language. The patient must read and examine the contents of this form before signing and dating it and he or she must be given a signed copy. No patient may be enrolled in a study before giving his or her informed consent.

The investigator may withdraw the trial drug at any time if he considers that this is in the patient's interest. The patient also has the right to withdraw his or her consent at any time (for the procedure to be followed in the case of premature discontinuation, see section 7.6 "Premature discontinuation").

The investigator must accept to inform all the patients included in the study about any new information on the trial drug discovered during the study in accordance with the recommendations of the sponsor and the IEC/IRB.

### **9.3 Data confidentiality**

All the data collected will be processed in a manner guaranteeing the strictest confidentiality. Patients will be informed that the data collected during the study will be archived and processed in accordance with local individual data protection law.

Patients will also be informed that clinical research monitors appointed by the sponsor, Health Authority Inspectors and IEC/IRB members may only obtain access to the source clinical data to check the data in the case report form. This point must be explicitly stated on the consent form.

The investigator must hold an updated list of all patients selected/enrolled in the study by noting the patient's initials in the same way as in the case report form together with the treatment and randomisation number where applicable.

### **9.4 Insurance**

A specific insurance was contracted to cover the civil liability of the investigators and sponsors working in therapeutic biomedical research.

## **10 ADMINISTRATIVE PROCEDURES**

By signing the study protocol, the investigator accepts to comply with the following points:

### **10.1 Regulatory aspects**

The study will be conducted in compliance with the current provisions of the German Drug Law and GCP Regulation (GCP-V), the respective decrees and the European Clinical Trial Directive. Regulatory reporting requirements will be agreed on by the parties in the investigator contract.

## **10.2 Quality Assurance**

The sponsor has to implement Quality Control and Quality Assurance systems to ensure that the study will be conducted according to Good Clinical Practices.

### **10.2.1 Monitoring**

Organization and monitoring of the study will be performed by acromion GmbH, Frechen, Germany, under the responsibility of the study sponsor. The study sites have to be monitored regularly. A monitoring guideline will be established by acromion before the initiation visit. The monitoring visits will take place in regular intervals to ensure that the study will be conducted in compliance with the GCP guidelines.

The study monitor is responsible for setting up the study and follow-up (visits, telephone calls, letters, and fax).

The study monitor will visit study centres in order to check that the case report forms are filled in without omission. The monitor will also control the progress of patient inclusion and make sure that the study treatments are stored, dispensed and accounted for according to the specifications given. The investigator must be available to help the clinical monitor during visits.

The monitor is responsible for reviewing it and clarifying and resolving any data queries during his/her next visit on site. The completed and corrected case report forms for completed visits will be collected by the monitor. A copy of the case report form must be kept by the investigator, who will ensure that it is kept safely with the other study documents such as the protocol, investigator's brochure and any protocol amendments.

Any suspicion of fraud has to be documented and the monitor has to inform the coordinating investigator and / or the sponsor. An audit of the centre will be performed as soon as possible to support or invalidate the suspicion. Based on the audit findings, the coordinating investigator will take appropriate measures.

### **10.2.2 Data Monitoring and Safety Committee (DMSC)**

An independent Data Monitoring and Safety Committee (DMSC) consisting of clinical and statistical experts will be established by the sponsor to review the interim efficacy and safety results. The DMSC meets regularly at three months intervals and if necessary. The DMSC will have access to unblinded data. Based on the results of the interim analysis the DMSC will give written recommendations to the sponsor to continue, to modify, to put on hold or to stop the trial.

The DMSC will act according to its own SOP and will prepare written minutes of its meetings. In order not to disseminate unblinded data and to ensure that all staff involved in the conduct of the study remains blind to the results of the interim analysis, only the members of the DMSC and the unblinded statistician will have access to these data.

### 10.2.3 Source Data Definition and Verification (SDV)

Source data are the original records of all variables collected for the trial. They include, but are not limited to:

- Signed informed consent
- Laboratory reports
- Individual patient clinical notes
- Hospital charts or pharmacy records and any other similar reports and records of any procedure performed in accordance with the protocol
- Details concerning inclusion and exclusion criteria
- Appropriate sections of the CRFs, where data is recorded directly onto specific forms

The CRF is the source document for all data where no other source exists such as body weight, blood pressure and physical examination.

The investigator must allow access to the important documents in the medical file to confirm their consistency with the case report form entries. No information on patient identity is allowed in these documents. The following must be checked: existence of informed consent, adherence to in-/exclusion criteria, tabulation of adverse events and completion of the primary safety and efficacy variables. Other checks that the data given in the case report forms complies with the source document will be carried out in accordance with the study specific monitoring plan.

